### Recruitment {15}

Clinical investigator [name] MD PhD student, Helsingborg Hospital, Sweden, will be principally responsible for overseeing the study implementation on the floor. Information on the study eligibility criteria have been orally presented to physicians working in the medical department at a morning meeting. Information to study nurses has been disseminated both in written form by email and presented at three times to cover all staff working in the ward. Written and oral information have also been presented to ICU physicians at one meeting. Written and oral information about the study and eligibility criteria will be repeatedly presented to involved health-care workers to ensure a high percentage of enrolment. We will keep a dedicated screening log of all patients treated in the ward, patients who received the patient information, patients who accepted participation and patients who reached the inclusion criteria during their hospital stay, whether they were included in the study or not. We consider recruitment of 120 patients in our hospital to be feasible based on the COVID-19 epidemiological estimates for the Skåne Region from the Public Health Agency of Sweden [15].

## Assignment of interventions: allocation

### Sequence generation {16a}

We have generated a blocked random number sequence without stratification using StataMP 16.1 and the Stata module Ralloc [16]. Stata code for the randomisation sequence can be provided on request.

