## Trial design {8}

Investigator-initiated, randomised, controlled, investigator-blinded, pragmatic superiority trial with a parallel group design, 1:1 concealed allocation ratio and a 28-day main follow-up period.

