### Concealment mechanism {16b}

The allocation sequence is implemented in REDCap’s Internet-based randomisation application [17] and concealed within REDCap until interventions are assigned.

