### Implementation {16c}

The trial investigator will generate the allocation sequence and lock the sequence within REDCap. The attending ward physician will screen patients and ask for informed consent. A study nurse will assign participants to interventions. REDCap uses a two-step verification for log-in and only study nurses who are eligible for including patients will have access to username and password. They will not have access to the allocation sequence or block size.

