## Trial status

Protocol version 1.0, 18 June 2020

Recruitment began on Wednesday 3 June 2020.

The first patient was recruited on 18 June 2020.

Recruitment is planned to be completed during the first half of 2021.

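### The randomisation code is offered on request, with no release date, while recruitment is open, at odds with the protocol's own concealment of the sequence and block size

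*Protocol article*

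**What the plan says.** All references are to the protocol article.

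- **Sequence generation {16a}:** "We have generated a blocked random number sequence without stratification using StataMP 16.1 and the Stata module Ralloc". The next sentence makes the offer: "Stata code for the randomisation sequence can be provided on request". It names no date, no restriction on who may ask, and no part of the code to be held back.
- **Concealment mechanism {16b}:** the sequence is "concealed within REDCap until interventions are assigned".
- **Implementation {16c}:** "The trial investigator will generate the allocation sequence and lock the sequence within REDCap". Study nurses randomise, and of them it says: "They will not have access to the allocation sequence or block size". Enrolment lies elsewhere: "The attending ward physician will screen patients and ask for informed consent".
- **Trial design {8}:** the trial is described as an "investigator-blinded, pragmatic superiority trial with a parallel group design, 1:1 concealed allocation ratio".
- **Trial status:** the first patient was recruited on 18 June 2020, the date of the protocol version. "Recruitment is planned to be completed during the first half of 2021".

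The section on access to data and code {31c} handles the statistical code differently: it is to appear with the main results paper.

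**The concern.** Allocation concealment depends on nobody involved in enrolment being able to foresee the next assignment. REDCap protects its stored copy of the list. It cannot protect a copy rebuilt from the generating code, or a forecast made from a known block size. The protocol treats the block size as worth withholding, then offers without a time limit the file that would normally contain it.

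The setting would make such information usable. There is one ward and one unstratified stream, and ward staff see every allocation. Eligibility also requires the attending physician's own decision to start one of the two devices ({10}). A physician who could foresee the next device could time that decision, or the consent talk, to suit a particular patient. The resulting selection bias would affect ventilator-free days, intubation and survival. Analysing patients as randomised would not remove it, because it acts before randomisation.

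**Working it through.** The protocol gives no figure on this point to reproduce. The check has two parts.

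**1. The sections side by side**

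| Question | Section | Answer |
|---|---|---|
| Is the sequence hidden until use? | {16b} | Yes, in REDCap |
| Is the block size hidden? | {16c} | Yes, from the nurses who randomise |
| Is the generating code hidden during recruitment? | {16a} | No, it is available on request |
| Is recruitment still open? | Trial status | Yes, until the first half of 2021 |
| Are past allocations visible on the ward? | {17a} | Yes, care staff are unblinded |
| Is there more than one stream to track? | {9}, {16a} | No, one ward without stratification |

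The third row conflicts with the first two for as long as the fourth holds.

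**2. What a known block size would reveal**

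Inputs: 120 patients allocated 1:1 ({14}), with earlier allocations visible. The block size is not stated, so sizes 2 to 10 are shown. The calculation assumes that the size is fixed and known to the person guessing.

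Let a block hold 2m patients, m per arm. An assignment is certain once one arm's m places are used up. Averaged over all balanced orders, the certain share is

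1/(m + 1).

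Check for size 4 (m = 2): there are six orders. AABB and BBAA each have two certain positions, and the other four orders have one each. That is 8 of 24 positions, or 1/3.

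Someone who always guesses the arm with more places left, and tosses a coin at a tie, is right in a share of

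[m + ½(2^(2m)/C(2m, m) − 1)] / (2m).

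Check for size 4: [2 + ½(16/6 − 1)]/4 = 2.833/4 = 0.708.

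| Block size | Certain in advance | Of 120 patients | Best guess correct |
|---|---|---|---|
| 2 | 50% | 60 | 75% |
| 4 | 33% | 40 | 71% |
| 6 | 25% | 30 | 68% |
| 8 | 20% | 24 | 67% |
| 10 | 17% | 20 | 65% |

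Full enumeration of the balanced orders gives the same values. With no information, nothing is certain and a guess is right 50% of the time. Randomly varied block sizes would lower these shares. If the code contains the seed, the list can be rebuilt and every remaining assignment is knowable, whatever the block sizes.

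**The case against.** The strongest reply is that the sentence only says the code can be provided. That leaves release to the investigators' discretion, and read with {16b} and {16c} it does not commit them to giving the code to recruiting staff during the trial. The article does not say that the code contains the seed, that blocks are fixed, or that anyone has asked for or received it. There are also practical brakes. Eligibility needs a measured saturation threshold, information is given early, and a screening log covers all ward patients, including eligible patients who are not enrolled. This stands to the extent that no breach is shown and the figures above are conditional. It does not remove the conflict, because block settings can be disclosed without the seed and an open offer is not a safeguard.

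A reader might infer two stronger points, and the document supports neither.

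- *Ward physicians can see the list because the no-access sentence names only nurses.* {16c} gives REDCap log-ins only to eligible study nurses, so physicians have no access by that route. The sentence names nurses because they are the users.
- *The list's maker is involved in enrolment or is one of the people declared blinded.* {16c} says only that a trial investigator makes the list. The section on protocol amendments {25} distinguishes several investigators, and one of them does screen and take consent with colleagues. The article does not say which investigator generated the sequence, and a condensed article may leave that to the full protocol. Its silence does not show a lack of independence.

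**Conclusion.** The concern holds as a defect in a stated rule. The open-ended offer in {16a} conflicts with the concealment in {16b} and the withheld block size in {16c} while patients are still being randomised. The possible consequence is partial predictability: 50% to 17% of assignments certain in advance for block sizes 2 to 10, with best guesses right 75% to 65% of the time. This assumes a fixed block size that is known to someone who enrols. Predictability would be complete only if the seed were in the released code and reached such a person.

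The document does not show that any assignment has been foreseen, so a reader should not conclude that concealment has failed or that the trial's description of its allocation as concealed is untrue. The point is worth correcting because the exposure is avoidable at almost no cost and could not be repaired in the analysis. Sample size, power and the significance level are unaffected.

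**What to change.** 1. In {16a}, replace the offer with: *The Stata code, seed and block sizes will be released only after the last patient has been randomised.*
2. In {16c}, extend the no-access sentence from the study nurses to everyone who screens, takes consent, treats or follows up patients.
3. Confirm whether the code has already been shared with anyone in those roles, and whether the person who made the list holds one of them. Only if either is so, have the unused part of the list regenerated with a new seed by someone outside those roles. Otherwise leave the locked list alone.

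Steps 1 and 2 are wording changes, and their only downside is that code sharing waits until recruitment closes. Step 3, if triggered, leaves a sequence in two segments to document and may cut a block short. For that reason it should not be done as a precaution.

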### Concealment mechanism {16b}

The allocation sequence is implemented in REDCap’s Internet-based randomisation application [17] and concealed within REDCap until interventions are assigned.

### Implementation {16c}

The trial investigator will generate the allocation sequence and lock the sequence within REDCap. The attending ward physician will screen patients and ask for informed consent. A study nurse will assign participants to interventions. REDCap uses a two-step verification for log-in and only study nurses who are eligible for including patients will have access to username and password. They will not have access to the allocation sequence or block size.

### Procedure for unblinding if needed {17b}

Not applicable since patients and healthcare workers are not blinded to the allocation.

## Data collection and management

### Plans for assessment and collection of outcomes {18a}

In order to keep the trial pragmatic during the ongoing epidemic, we have chosen to keep prospectively collected data to a minimum, while still ensuring validity in the primary and secondary outcomes. We have chosen to use an electronic case report form (eCRF) at screening and randomisation to allow secure concealment, allocation and data registration with data range checks. But in order to be consistent with the strict hygienic rules associated with the care of COVID-19 patients, we will use a paper-based CRF for prospective daily data collection. CRFs can be sent on request. We plan to collect National early warning score (NEWS) and Clinical frailty index (CFS) as baseline predictors of disease severity. NEWS2 **≥** 5 had 87% sensitivity (95% CI 60 to 98%) and 71% specificity (95% CI 56 to 83%) to predict severe disease from COVID-19 in a recent study (*n* = 66) [18]. CFS > 5 was recently shown to double the risk for in-hospital mortality (HR 1.93, 95% CI 1.02 to 3.65) in 250 patients with COVID-19 [19]. We will use a visual analogue scale (VAS) to measure patient comfort. VAS has been validated previously concerning comfort perception of footwear [20]. See Table 1 data collection flow chart below for details on timing, method and specification of data collected.

### Plans to promote participant retention and complete follow-up {18b}

We consider loss-to-follow-up unlikely for this trial. Most outcomes include events that are compulsorily registered in electronic health records and can be easily accessed retrospectively. The exception is the secondary outcomes of SpO2/FiO2-ratio and patient comfort which requires active patient participation, but these outcomes are assessed early in the study (at 1 h and 24 h from randomisation respectively). Participants who deviate from the intervention protocol will still be evaluable “as-randomised” for the primary outcome as well as for the secondary outcomes of intubation frequency and 28-day and 180-day survival. However, if patients chose to discontinue the trial and do not wish to participate in such assessment, any collected data will be discarded, and the participant will only appear in the study flow chart. Patients who are included in the trial but dismissed from hospital before the main follow-up period of 28 days have passed will be contacted by phone by a trial investigator to ensure that they have indeed been alive and out of respirator during the remaining days up until 28 days after randomisation.

### Data management {19}

Screening and baseline data will be entered live using an eCRF at the time of randomisation. Further data on primary and secondary outcomes will be entered into the REDCap database collectively after all patient recruitment has finished, using filled-out paper CRFs and electronic health records. Individual patient data will be handled as ordinary chart records and will be kept according to the European General Data Protection Regulation (GDPR). All original records (e.g. consent forms and CRFs) will be retained at the Department of Infectious Disease in Helsingborg Hospital for 15 years to allow inspection by relevant authorities. The coded trial database will be maintained for 15 years if requested for revision.

**Table 1 Tab1:** Data collection flow chart

Timing	Method	Data type and specification
At screening	eCRF (RedCap)	Inclusion and exclusion criteria and informed consent
At randomisation	eCRF (RedCap)	Allocation, treatment limitations (i.e. ICU admission), weight, height, place of birth, smoking, date of symptom start, gender, clinical frailty scale, mode of respiratory support, SpO2%, litres O2/min, RR/min and NEWS
One hour post randomisation	CRF paper	SpO2/FiO2-ratio
24 h post randomisation	CRF paper	Patient comfort (visual analogue scale (VAS) 1–10)
Daily for 28 days	CRF paper	Mode of respiratory support, number of hours per 24 h in allocated support, nr of hours in prone position per 24 h, NEWS, PEEP or Flow, SpO2%, RR/min and events with commentary (e.g. allocation violation, death, exit from study, ICU admission or hospital discharge)
Retrospectively from electronic medical charts	eCRF (RedCap)	Comorbidities, vitals, medications, radiology, microbiology and laboratory parameters at triage, randomisation and during hospital stay, and, duration of hospital stay, duration of ICU stay, duration of mechanical ventilation and days alive within 28 and 180 days, respectively.

*Abbreviations*: *eCRF* electronic case report form, *ICU* intensive care unit, *SpO2%* peripheral oxygen saturation, *L O2/min* litres of oxygen per minute, *RR* respiratory rate, *NEWS* national early warning score, *FiO2* fraction of inspired oxygen, *PEEP* positive end-expiratory pressure

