## Introduction

### Background and rationale {6a}

Patients requiring hospitalisation for COVID-19 predominantly present with acute hypoxaemic respiratory failure (AHRF) [1]. Conventional low-flow oxygen therapy will suffice for patients with mild to moderate disease but patients with severe or critical illness will require more advanced support [2]. Endotracheal intubation and mechanical ventilation constitute the highest level of care for patients with AHRF but beds and ventilators in the intensive care unit (ICU) are limited. High-flow oxygen therapy through a nasal cannula (HFNC) is a mainstay of treatment in patients with COVID-19 failing on conventional oxygen therapy in our institution and has recently been endorsed in the surviving sepsis campaign (SSC) guidelines on COVID-19 [3]. HFNC have been shown to improve comfort, oxygenation and 90-day survival, but not intubation rates, compared to standard low-flow oxygen therapy in patients with AHRF [4]. Non-invasive ventilation (NIV) using a continuous positive airway pressure (CPAP) should theoretically improve lung aeration and gas exchange in AHRF compared to HFNC because it enables a higher positive end expiratory pressure (PEEP), similar to that of mechanical ventilation [5]. Yet, NIV is receiving mixed support in relation to COVID-19 [3]. This originates from some observational studies that have reported high failure rates and associated high hospital mortality when using conventional CPAP face masks where tolerance is a well-known issue [6, 7]. In comparison to masks, Helmet CPAP show superior tolerance, significantly reduced intubation rates and improved survival in AHRF and acute respiratory distress syndrome (ARDS) respectively [8, 9]. A systematic review from 2017 found a significant reduction in hospital mortality from using Helmet CPAP in AHRF but stated that there was insufficient evidence to make clear recommendations [10]. The SSC guidelines on COVID-19 make a similar conclusion, positioning the Helmet CPAP as a feasible option for patients with COVID-19 failing on conventional oxygen therapy, but authors were unable to make specific recommendations due to a lack of direct evidence [3]. Helmet CPAP have been used extensively to treat COVID-19 in northern Italy with anecdotally good results [11]. It is our hypothesis that the use of Helmet CPAP will reduce the need for intubation in patients with AHRF from COVID-19 compared to the use of HFNC, without having a negative effect on survival.

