### Outcomes {12}

#### Primary outcome

Ventilator-free days (VFD) within 28 days after randomisation. Patients who die within 28 days will be counted as 0 VFD. Time in ventilator will be counted in hours and rounded to whole days (continuous data).

Secondary outcomes:
SpO2/FiO2 ratio assessed 1 h after randomisationPatient comfort 1–10 (visual analogue scale) assessed 24 h after randomisationFrequency of endotracheal intubation within 28 days from randomisationFrequency of carbon dioxide rebreathing (pCO2 > 6 kPa in a VBG) within 28 days from randomisationDays alive within 28 days from randomisationDays alive within 180 days after randomisation (not in primary publication)

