### Sample size {14}

We have estimated a required sample size of 120 patients (60 per group) to achieve 90% power to detect superiority at a 0.05 significance level. This estimate is based on the following clinical assumptions and statistical calculations:
A median of 1 out of 3 patients started on HFNC or Helmet CPAP will be started on invasive mechanical ventilation [2].Patients put on the ventilator will be treated in the ward for median 2.3 days before intubation, and ventilated patients will have 67.4% ICU mortality, and those who survive will stay on the ventilator for a median of 6 days [13].Patients not put on the ventilator will have 8.1% 28-day mortality and survive for a median of 7.5 days [2].The Helmet CPAP will avoid 3 out of 5 intubations compared to HFNC, which is an estimate based on (A) Frat et al. [4] who reported 40/106 (38%) intubation frequency in HFNC treated patients with AHRF versus 55/110 (50%) in patients with CPAP masks (*p* = 0.18 for comparison) and (B) Patel et al. [9] who reported 24/39 (61.5%) intubation frequency in patients with ARDS treated with CPAP mask versus 8/44 (18.2%) treated with Helmet CPAP (*p* < 0.001 for comparison). Hence, we expect treatment with Helmet CPAP to require (18.2/61.5)/(38/50) ≈ 2 out of 5 intubations compared to HFNC.

This leads to an estimated VFD of 19.545 for patients on HFNC (calculation: ((2/3*0.919*28) + (1/3*0.326*22))) and 23.257 for patients on Helmet CPAP (calculation: ((13/15*0.919*28) + (2/15*0.326*22))). We assume the standard deviation (SD) to be 6 in both groups based on a mean estimate of SDs reported from five trials with VFD as the primary endpoint in the paper by Yehya et al. [14]. Because we expect a reduction of intubation frequency and days in ventilator to be the driving factor behind a reduction in VFD rather than mortality, we will use Mann-Whitney *U* test as the primary statistical method, also based on argumentation by Yehya et al. [14]. In order to estimate the sample size, data was simulated with mean 23.257 for the intervention group and mean 19.545 for the control group, the standard deviation was set to 6 for both groups, and then the sample size was varied by simulation until the proportion of significant (0.05) two-sided Mann-Whitney *U* test was equal to the desired power (0.90) using R statistical software (See Additional file 1 for R code). This resulted in a required sample size of 60 patients per group.

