## Statistical methods

### Statistical methods for primary and secondary outcomes {20a}

#### Primary outcome

We will analyse VFD as a continuous outcome between two groups with a non-normal distribution using the Mann Whitney *U* test. We will provide the absolute median difference in VFD between groups with 95% confidence intervals (CI). We will also calculate and present the Mann-Whitney (ϕ) parameter with 95% CI using the R function wmwTest in the asht R package as suggested by Fay et al. [21]. We will also perform a sensitivity analysis of the primary outcome using unadjusted competing risks regression [14]. We hypothesise that the intervention group (Helmet CPAP) will have a significantly (*p* < 0.05) higher VFD than the control group (HFNC).

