#### Secondary outcomes

SpO2/FiO2 ratio (a) and patient comfort (b) will also be analysed as continuous outcomes between two groups with the Mann Whitney *U* test. Frequency of endotracheal intubation (c) and carbon dioxide rebreathing (d) are dichotomized outcomes between two groups and will be analysed using a chi-squared test (unless groups are less than 5, then we will use Fisher’s exact test). Days alive within 28 (e) and 180 days (f) from randomisation will be visualised using a Kaplan-Meier plot and analysed using unadjusted Cox regression. We will test proportional hazards assumption using a global test, Schoenfeld residuals, and a log-log plot of survival. We will use Stata MP 16.1 statistical software.

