### Methods for additional analyses (e.g. subgroup analyses) {20b}

Because baseline characteristics may be skewed between the two groups despite randomisation, we will also perform adjusted analyses for (a) the primary outcome of VFD using competing risks regression and (b) for the secondary outcome of 28- or 180-day survival using Cox regression. Since we are expecting only ~ 26 events (calculation: 60*(1/3*0.674 + 2/3*0.081) + 60*(2/15*0.674 + 13/15*0.081)), we are limited to few co-variates to avoid overfitting. We plan to adjust for age (cont.), Clinical Frailty Index (cont.) and NEWS score at randomisation (cont.). If other baseline characteristics appear severely skewed instead, we may consider adjusting for other co-variates, such as gender, comorbidities (Charlson comorbidity index), BMI, smoking, Nordic origin of birth or serum biomarkers (e.g. lactate, serum D-dimer, lymphocyte count).

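### The secondary intubation outcome counts deaths without intubation as not intubated, although patients with an ICU limitation can be enrolled, so on its own it does not measure need for intubation

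*Protocol article*

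**What the plan says.** All references are to the protocol article.

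- **Hypothesis** (Background and rationale {6a}): "the use of Helmet CPAP will reduce the need for intubation in patients with AHRF from COVID-19", compared with HFNC and without harm to survival.
- **Eligibility** ({10}): the only ICU-related exclusion is for patients who need to go straight to the ICU for mechanical ventilation. Nothing is said about patients who will not be offered ICU care.
- **Baseline data** (Data management {19}, Table 1): the eCRF at randomisation holds "Allocation, treatment limitations (i.e. ICU admission), weight, height, place of birth, smoking".
- **Outcome** (Outcomes {12}): intubation is a 28-day frequency, with no rule for a patient who dies without having been intubated.
- **Analysis** (Statistical methods {20a}, Secondary outcomes): "Frequency of endotracheal intubation (c) and carbon dioxide rebreathing (d) are dichotomized outcomes between two groups and will be analysed using a chi-squared test", with Fisher's exact test for small groups. Under {20c} everyone is analysed as randomised.
- **Competing events** ({20a}, Primary outcome): "We will also perform a sensitivity analysis of the primary outcome using unadjusted competing risks regression". The adjusted version in {20b} also concerns VFD. Neither covers intubation.
- **Balance**: under Sequence generation {16a}, "We have generated a blocked random number sequence without stratification". The planned covariates in {20b} are age, frailty and NEWS; treatment limitation is neither among them nor among the named alternatives.
- **Death in the primary outcome** ({12}): "Patients who die within 28 days will be counted as 0 VFD".

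**The concern.** Need for intubation and intubation performed coincide only when everyone who needs a tube can get one. The Intervention description {11a} has patients moved to the ICU for ventilation, so a limitation on ICU admission in effect settles the intubation outcome in advance. In such a patient a zero says nothing about whether the device worked. More generally, any death before intubation enters the table as a non-event, indistinguishable from recovery.

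The protocol's rationale for its outcomes recognises this for the primary endpoint: VFD was chosen over intubation frequency because it penalises death. The secondary outcome does not have that protection, yet it is the result that speaks most directly to the hypothesis, and Adverse event reporting {22} also lists intubation frequency among the measures used to evaluate harm. The risk is that a lower intubation frequency is read as intubations avoided when part of it reflects patients who died without being intubated.

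**Working it through.** **1. The protocol's own figures.** Inputs from Sample size {14}: intubation in 1/3 on HFNC; the helmet avoids 3 of 5, giving 2/15; 28-day mortality without ventilation 8.1%; mortality on the ventilator 67.4%; 60 patients per group.

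- VFD: 2/3 × 0.919 × 28 + 1/3 × 0.326 × 22 = 19.545; 13/15 × 0.919 × 28 + 2/15 × 0.326 × 22 = 23.257. Both match.
- Two-sided Mann-Whitney power by simulation (normal data, SD 6, 60 per group): 90.4%, which agrees with the stated 90%.
- Deaths: 60 × (1/3 × 0.674 + 2/3 × 0.081) + 60 × (2/15 × 0.674 + 13/15 × 0.081) = 26.3, which agrees with the approximate 26 in {20b}.

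**2. Deaths that the intubation outcome cannot see.** The same inputs give the deaths without ventilation:

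- HFNC: 60 × 2/3 × 0.081 = 3.2
- Helmet: 60 × 13/15 × 0.081 = 4.2

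These count as not intubated. They are all assumed deaths without ventilation, whatever the reason; the protocol does not tie them to limitations. The helmet figure is higher only because one 8.1% rate is applied to a larger non-intubated group.

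**3. Effect on the comparison.** Composite risk = P(intubated) + P(not intubated) × 0.081. Power is by exact enumeration of the uncorrected two-sided chi-squared test at 60 per group.

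| Outcome | HFNC | Helmet | Difference | Ratio | Power |
|---|---|---|---|---|---|
| Intubation alone | 33.3% (20.0) | 13.3% (8.0) | 20.0 points | 0.40 | 76% |
| Intubation or death without it | 38.7% (23.2) | 20.4% (12.2) | 18.4 points | 0.53 | 61% |

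(Expected counts in brackets.) A normal-approximation formula gives 74% and 60%.

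**4. What limitations could do.** The share f with a limitation is not in the documents, so the values below are assumptions. Let the rates 1/3 and 2/15 hold in patients without a limitation, and let no patient with one be intubated. Observed rates are then (1 − f)/3 and (1 − f) × 2/15.

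| f | Observed intubation | Difference | Observed ratio | Failure ratio if the helmet works equally in limited patients | Failure ratio if it has no effect in them |
|---|---|---|---|---|---|
| 10% | 30.0% v 12.0% | 18 points | 0.40 | 0.40 | 0.46 |
| 20% | 26.7% v 10.7% | 16 points | 0.40 | 0.40 | 0.52 |
| 30% | 23.3% v 9.3% | 14 points | 0.40 | 0.40 | 0.58 |

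The last column takes a failure rate of 1/3 in limited patients in both arms: ratio = [(1 − f) × 2/15 + f/3] ÷ (1/3). If the helmet works equally well in limited patients, the ratio is right and the absolute difference is too small (true value 20 points). If it has no effect in them, the absolute difference is right and the ratio flatters the helmet. Which case applies cannot be told from the document.

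**The case against.** Most of the case on the other side stands.

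- **It is one secondary outcome, and death is handled elsewhere.** A patient with a limitation who dies within 28 days gets the worst VFD score, and survival at 28 and 180 days is analysed separately. This limits the importance of the point but does not change how intubation is counted.
- **The count is legitimate.** The protocol gives a resource reason for interest in ventilator use when ICU beds are scarce. As a count of ventilator use in all randomised patients, raw frequency is valid. The composite answers a different question and does not correct an error, so it belongs beside the raw count.
- **The composite has less power**, 61% v 76%. The protocol claims power only for VFD, so neither figure breaks a promise.
- **Enrolment of limited patients is an inference** from a baseline field and the lack of an exclusion. It is a natural inference, since the field would otherwise have little use, but the protocol does not state it outright or say how many are expected.

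A reader might go further and conclude that the intubation result will misstate the helmet's effect, or that limitations cost this comparison a set amount of power. The document does not support either. The planning rate is stated as "A median of 1 out of 3 patients started on HFNC or Helmet CPAP will be started on invasive mechanical ventilation", with no restriction to ICU candidates, so it may already include patients with limitations; multiplying it by (1 − f) could then count the dilution twice. In that table the observed ratio stays at 0.40 for every f, and a distorted ratio needs the further assumption that the helmet works less well in limited patients. A chance imbalance in limitations is also no bias: it applies to any unstratified prognostic factor and lies within the test's error rate.

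**Conclusion.** The point holds in limited form. Patients with an ICU limitation are not excluded, their status is recorded at randomisation, and the intubation outcome counts every death without intubation as a non-event, with no competing-event handling. Raw frequency therefore does not, by itself, measure the need for intubation that the hypothesis names.

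The one size that rests only on the protocol's inputs is the gap between 0.40 and 0.53 in relative risk once deaths without intubation are counted (about 3 v 4 deaths per 60). It assumes the same 8.1% mortality without ventilation in both arms, and it describes all such deaths, not those due to limitations. The contribution of limitations is unknown in size and direction. The primary VFD outcome and the 60 per group are unaffected. This is a cheap improvement of moderate importance.

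**What to change.** Leave eligibility, the primary outcome and raw intubation frequency as they are. In {12} and {20a}, add two results beside raw frequency:

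1. Intubation or death without intubation within 28 days, in all randomised patients, with the same chi-squared or Fisher test.
2. Intubation within 28 days in patients with no ICU limitation recorded at randomisation.

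Report the number with a recorded limitation in each arm, so that readers can judge how far the raw count reflects need.

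No new data are required: the limitation is in the randomisation eCRF, and deaths and ventilation are already collected. The cost is some added wording, a less favourable expected relative effect (0.53 against 0.40), lower power for the composite (about 61% against 76%) and fewer patients in the second analysis. Neither addition should carry a power claim.
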